### 7.2 POWER CALCULATIONS

Sample size for the study was calculated based on our pilot data evaluating patients undergoing pancreaticoduodenectomy with an ERAS program at Austin hospital. With a median length of hospital stay of 16 days, and a SD of 4 days, if we were to demonstrate a mean difference between the control group and the GDT group of 2 days, with a power value

of 80%, we require a minimum of 21 patients to be recruited into each group. We will recruit 5 additional patients in each group, given the large SD.

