### **Summary of power calculations for this study**

|                                        |                |     |                |                                    |
|----------------------------------------|----------------|-----|----------------|------------------------------------|
| Confidence Interval (2-sided)          |                | 95% |                |                                    |
| Power                                  |                | 80% |                |                                    |
| Ratio of sample size (Group 2/Group 1) |                | 1   |                |                                    |
|                                        | Group 1 |     | Group 2 | Mean difference |
| Mean                                   | 16             |     |                | 2.5                                |
| Standard deviation                     | 4              |     | 0.0            |                                    |
| Variance                               | 0.0            |     | 0.0            |                                    |

|                        |    |  |
|------------------------|----|--|
| Sample size of Group 1 | 21 |  |
| Sample size of Group 2 | 21 |  |
| Total sample size      | 42 |  |

 Mean difference= (Group 1 mean) - (Group 2 mean)

*RESULTS FROM OPENEPI, VERSION 2, OPEN SOURCE CALCULATOR--SSMEAN*

<http://www.openepi.com/OE2.3/SampleSize/SSMean.htm>

Source file last modified on 09/21/2010 13:10:35

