## **7.3 STATISTICAL METHODS TO BE UNDERTAKEN**

Statistical analysis will be performed using computerized software (SPSS for Windows version 12.0). For data that was non-normally distributed a Mann–Whitney test was used and normally distributed data were compared using the Student T test. Ordinal and nominal data were compared using Chi square analysis. A p-value <0.05 will be considered significant. Standard statistical tests will be used, and an independent statistician blinded to the randomisation will undertake all statistical analyses.

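### The 21 per group comes from a standard deviation of 0.0 in one arm and a 2.5-day difference; with SD 4 in both arms, 26 per arm has about 42% power for the stated 2 days, not 80%

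*Protocol*

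**What the plan says.** Section 7.2 of the protocol bases the sample size on the institution's pilot data: "With a median length of hospital stay of 16 days, and a SD of 4 days". The target is set by the clause "if we were to demonstrate a mean difference between the control group and the GDT group of 2 days", and at 80% power the text concludes that "we require a minimum of 21 patients to be recruited into each group". Five patients per group are then added because the SD is considered large. Section 7.1 accordingly fixes enrolment at 26 per arm, 52 in all.

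The table headed Summary of power calculations for this study is the calculator output behind the 21. It shows a two-sided 95% interval, 80% power, a 1:1 ratio, a Group 1 mean of 16 and a mean difference of 2.5. Its SD row reads "Standard deviation | 4 | | 0.0", so the SD is 4 in Group 1 and zero in Group 2. It returns 21 and 21, total 42. Section 7.3 sets the test level: "A p-value <0.05 will be considered significant".

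**The concern.** Text and table disagree on two inputs. The target difference is 2 days in one and 2.5 days in the other. The text gives a single SD of 4, whereas the table gives the second group no variability at all. An SD of zero would mean that every patient in that group stays exactly the same number of days, and nothing in the protocol supports that.

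Both discrepancies push the required number down. Zero variance in one arm halves the variance sum and so halves n. Using 2.5 instead of 2 days multiplies n by (2/2.5)² = 0.64, a further cut of 36%.

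This is the only sample size calculation for the primary outcome made with the trial's own inputs. If it is wrong, the 80% power put to the ethics committee and to participants is one the design does not have, and a true 2-day benefit would more likely than not be missed.

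**Working it through.** **Inputs.** Two-sided alpha 0.05 (section 7.3 and the table); power 80%; 1:1 allocation; SD 4 (section 7.2); difference 2 days (text) or 2.5 days (table); Group 2 SD 0.0 (table); 26 per arm enrolled (section 7.1).

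**Formula.** For two means with separate variances, normal approximation:

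n per group = (z₀.₉₇₅ + z₀.₈₀)² × (SD₁² + SD₂²) / d², where (1.960 + 0.842)² = 7.849 before rounding of the z values.

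**Step 1: reproduce the protocol's figure.** With the table's inputs, d = 2.5, SD₁ = 4, SD₂ = 0:

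7.849 × (16 + 0) / 6.25 = 20.09, rounded up to 21.

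This matches the printed result, so the 0.0 was used in the calculation and is not merely a display fault.

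**Step 2: try the other combinations of the printed values.**

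| Difference (days) | SD, Group 1 / Group 2 | n per group, two-sided | n per group, one-sided |
|---|---|---|---|
| 2.5 | 4 / 0 | 20.09 → 21 | 15.83 → 16 |
| 2 | 4 / 0 | 31.40 → 32 | 24.73 → 25 |
| 2.5 | 4 / 4 | 40.19 → 41 | 31.65 → 32 |
| 2 | 4 / 4 | 62.79 → 63 | 49.46 → 50 |

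Among the values printed in section 7.2, only the first row, two-sided, gives 21. With the t distribution instead of the normal, the two-sided figures for SD 4 / 4 are 42 (2.5 days) and 64 (2 days).

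**Step 3: power of the planned size.** With SD 4 in both arms, the two-sided t-test has noncentrality d / (4 × √(2/n)). At n = 26 this is 1.803 for 2 days and 2.253 for 2.5 days.

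| n per arm | Power for 2 days | Power for 2.5 days |
|---|---|---|
| 21 | 35% | 51% |
| 26 | 42% | 60% |

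The normal approximation gives 37% and 53% at 21 per arm, and 44% and 62% at 26 per arm, so the choice of method does not matter here.

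**Step 4: what 26 per arm can detect.** At 80% power and SD 4 in both arms the detectable difference is 3.17 days by t-test. By the normal approximation it is 4 × √(2/26) × 2.802 = 3.11 days.

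**Step 5: take the zero SD literally.** With SD 4 / 0 and 26 per arm, the standard error is √(16/26) = 0.784. Power for 2 days is Φ(2/0.784 − 1.960) = Φ(0.590) = 72%. For 2.5 days it is Φ(1.227) = 89%. The claim made in the text, 80% for 2 days, fails even then.

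**The case against.** The strongest objection is that nothing in the protocol says outright that SD 4 applies to both arms, so the 42% rests on an assumption. That is true, and it should be labelled as one. It is the natural reading, because section 7.2 gives one SD and no reason for a different one under goal-directed therapy (GDT). It may also be generous: section 2.3 reports a median stay of 17 days with a range of 7 to 140 in 150 consecutive pancreaticoduodenectomies. The size of the shortfall depends on the assumption. Its existence does not, as step 5 shows.

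A second objection is that 26 are enrolled, not 21, and that section 7.1 offers another justification: a cited trial with a 3-day difference and SD 3 in each group. On those figures 26 per arm would have about 94% power, and with 3 days and SD 4 about 76%. But section 7.2 says that this trial was sized from its own pilot data for 2 days. The cited trial's standardised difference is 3/3 = 1.0, against 2/4 = 0.5 here, and halving it needs about four times the patients. What stands is that the protocol carries three differences (2, 2.5 and 3 days), and a correction must deal with section 7.1 too.

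The five extra patients per group do not close the gap, which is 63 − 26 = 37 per arm for 2 days and 41 − 26 = 15 for 2.5 days (one more each by t-test).

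It is also fair to say that the power figures are conditional. They assume a t-test and 26 analysable patients per arm. Section 7.3 allows a Mann–Whitney test, and sections 6.2 and 6.3 remove withdrawn and unblinded patients from analysis without replacing them. No rate is given for such losses, but they can only reduce power.

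**Conclusion.** The concern holds. The 21 per group was computed with no variability in the second group and for 2.5 days, and does not support the 2-day statement in the text. Assuming SD 4 in both arms, two-sided alpha 0.05 and all 26 per arm analysed, power is about 42% for 2 days against the 80% claimed. A sample of 63 to 64 per group would be needed for 2 days. No combination of the inputs printed in section 7.2 gives 80% two-sided power for 2 days with 21 or 26 per arm. Because this is the stated basis for the primary outcome, it must be corrected.

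**What to change.** In section 7.2 and its table:

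- Rerun the calculation with one target difference and the same non-zero SD in both groups, and use those inputs in both text and table.
- Delete the statement that 21 per group is the minimum.
- State what 26 per arm provides, with its conditions: for SD 4 in both arms, a two-sided t-test at 0.05 and no losses from analysis, about 42% power for 2 days, 60% for 2.5 days and 80% for about 3.2 days.
- Say in section 7.1 how the cited trial's 3-day difference and SD of 3 relate to this trial's target, so that only one target difference remains.
- Add that a non-significant result will be read from the confidence interval for the difference and treated as inconclusive where that interval still includes the target.

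The cost is protocol wording, a corrected table and a less favourable stated power. The correction itself needs no further patients. Raising the sample size towards 41 to 42 or 63 to 64 per group is a separate decision for the sponsor.

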### **Summary of power calculations for this study**

|                                        |                |     |                |                                    |
|----------------------------------------|----------------|-----|----------------|------------------------------------|
| Confidence Interval (2-sided)          |                | 95% |                |                                    |
| Power                                  |                | 80% |                |                                    |
| Ratio of sample size (Group 2/Group 1) |                | 1   |                |                                    |
|                                        | Group 1 |     | Group 2 | Mean difference |
| Mean                                   | 16             |     |                | 2.5                                |
| Standard deviation                     | 4              |     | 0.0            |                                    |
| Variance                               | 0.0            |     | 0.0            |                                    |

|                        |    |  |
|------------------------|----|--|
| Sample size of Group 1 | 21 |  |
| Sample size of Group 2 | 21 |  |
| Total sample size      | 42 |  |

 Mean difference= (Group 1 mean) - (Group 2 mean)

*RESULTS FROM OPENEPI, VERSION 2, OPEN SOURCE CALCULATOR--SSMEAN*

<http://www.openepi.com/OE2.3/SampleSize/SSMean.htm>

Source file last modified on 09/21/2010 13:10:35

## **7.3 STATISTICAL METHODS TO BE UNDERTAKEN**

Statistical analysis will be performed using computerized software (SPSS for Windows version 12.0). For data that was non-normally distributed a Mann–Whitney test was used and normally distributed data were compared using the Student T test. Ordinal and nominal data were compared using Chi square analysis. A p-value <0.05 will be considered significant. Standard statistical tests will be used, and an independent statistician blinded to the randomisation will undertake all statistical analyses.

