## 7. STATISTICAL METHODS

### 7.1 SAMPLE SIZE ESTIMATION & JUSTIFICATION

We will recruit 52 patients in total, 26 patients in the GDT group and 26 patients in the standard group.

This is in keeping with realistic power calculations used in other studies evaluating the use of GDT in patients undergoing major abdominal surgery. Canesson's group in the US detect a 3-day mean length of stay difference between the two groups, with a standard deviation of 3 days in each group, a two tailed alpha of 0.05 and power of 0.80, and calculated that a minimum of 17 subjects were required in each group. They assumed that a similar sample size would be needed to detect a similar difference in time to return of GI function. Also, since they expected similar results between arterial pressure waveform analysis technology used for their study and the oesophageal Doppler technology used for other referenced studies, it was felt that this estimation was appropriate.

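### Section 7.3 tests ordinal data with chi-square, which ignores the ordering; a rank or trend test would be a free, minor improvement

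*Protocol*

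**What the plan says.** Protocol section 7.3 sorts data by type and gives each type a test:

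- Normally distributed data go to Student's t test.
- For skewed data: "For data that was non-normally distributed a Mann–Whitney test was used".
- For categories: "Ordinal and nominal data were compared using Chi square analysis". No trend version of chi-square is named.
- The threshold is stated as "A p-value <0.05 will be considered significant".

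Section 7.1 plans "26 patients in the GDT group and 26 patients in the standard group". Under sections 6.2 and 6.3, withdrawn patients leave the analysis and are not replaced, so the analysed number can be smaller.

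Pain scores appear in section 4.4 among the additional data to be collected, with no scale, timing or planned comparison. They are absent from the primary and secondary outcomes in section 3.3.

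**The concern.** The rule puts ordered and unordered categories under one test. Pearson chi-square adds up squared deviations over the columns of the table, and the sum does not change if the columns are shuffled. With k levels it spreads the evidence over k-1 degrees of freedom. A steady shift of one arm towards better or worse scores gets no credit for being steady. With many levels and few patients the expected counts also become small, and the chi-square approximation becomes poor.

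The same section already names a test that uses the order, but assigns it elsewhere. What is at stake is power for any ordinal comparison between arms. A second cost is ambiguity: a pain score can be called ordinal (chi-square) or non-normal (Mann-Whitney), and the protocol does not settle which rule applies.

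**Working it through.** The plan gives no power figure for an ordinal measure, so there is none to reproduce. The sample-size calculation in section 7.2 concerns length of stay and does not enter here.

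**Inputs from the protocol.** 26 patients per arm, N = 52 (section 7.1); significance level 0.05 (section 7.3); two-sided (power summary table in section 7.2).

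**Assumptions, not in the protocol.** 2 to 11 levels; equal control-arm probabilities, plus one humped 0-10 scale with control-arm percentages 5, 8, 12, 15, 16, 14, 12, 8, 5, 3, 2; a proportional odds ratio (OR) of 3 or 4.

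**Step 1: model.** For each cut-point j, logit P(Y ≤ j | GDT) = logit P(Y ≤ j | control) + ln(OR).

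**Step 2: tests.**
- Pearson: X² = Σ(O − E)²/E on k − 1 degrees of freedom, empty columns dropped.
- Mann-Whitney: normal approximation with tie correction.
- Linear-by-linear trend: M² = (N − 1)r² on 1 degree of freedom, with r the correlation of arm and score.

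**Step 3: power.** 3,000 simulated trials per setting. The Monte Carlo standard error of each power is at most √(0.25/3000), or 0.9 points.

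| Levels | OR | Chi-square | Mann-Whitney | Loss (points) |
|---|---|---|---|---|
| 2 | 3 | 48.1% | 45.3% | none |
| 2 | 4 | 67.8% | 64.9% | none |
| 3 | 3 | 44.5% | 55.0% | 10.5 |
| 3 | 4 | 62.7% | 70.8% | 8.1 |
| 4 | 3 | 40.5% | 56.6% | 16.1 |
| 4 | 4 | 58.3% | 75.5% | 17.2 |
| 5 | 3 | 35.0% | 58.1% | 23.1 |
| 5 | 4 | 54.7% | 76.6% | 21.9 |
| 7 | 3 | 29.6% | 59.4% | 29.8 |
| 7 | 4 | 45.0% | 78.6% | 33.6 |
| 11, equal | 3 | 19.6% | 59.7% | 40.1 |
| 11, equal | 4 | 33.1% | 78.7% | 45.6 |
| 11, humped | 3 | 18.7% | 60.2% | 41.5 |
| 11, humped | 4 | 30.1% | 77.6% | 47.5 |

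With 3 or more levels the trend test is within about 1 point of Mann-Whitney throughout. A second simulation, with 4,000 trials per setting at OR 3, gave 40% against 57% for 4 levels, 36% against 59% for 5, and 17% against 59% for an 11-level score with an assumed spread.

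**Step 4: expected counts.** With equal levels and no effect, each cell expects 26/k patients: 26/5 = 5.2, 26/7 = 3.7, 26/11 = 2.4. In the simulations with 11 levels, 93% to 98% of expected counts were below 5 on the equal scale and about 90% on the humped scale.

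**Step 5: type I error with 11 levels.** Chi-square rejected in 3.1% (equal) and 2.3% (humped) of trials with no effect, and Mann-Whitney in 5.5% and 4.9%. Mann-Whitney stays close to the nominal 5%, so its advantage does not come from a materially inflated error rate.

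**Step 6: fewer patients.** At 21 per arm (11 equal levels, OR 3) power is 12.9% against 51.4%. The pattern is the same.

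**The case against.** The strongest reply is that the sentence may touch nothing that matters. No listed outcome is identifiably ordinal: the outcomes are durations, haemodynamic values, fluid and drug amounts or types, transfusion, and named complications. Pain is only collected data, and an analyst could treat it as non-normal and use Mann-Whitney. The wording names no variant of chi-square, so a trend version is not strictly excluded. The levels, distributions and odds ratios above are assumed, and a proportional-odds shift is the pattern that suits a rank test. All of this stands, and it limits the point to a minor one. It does not remove it, because the written rule still sends ordinal data to the test for unordered categories.

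A reader might infer more than the documents support:

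- **That a real shift would usually be missed.** At OR 4 with 3 to 5 levels, chi-square still has 55% to 63% power. At OR 2.5, Mann-Whitney itself reaches only 42% to 45% in the second simulation (4, 5 and 11 levels). Part of the problem is the sample size.
- **That the lost power cannot be recovered.** The data are kept, and the test can be reassigned before unblinding.
- **That ASA class or complication grades are affected.** ASA class is a baseline variable with at most three levels here, since classes IV and V are excluded (section 5.3). Complications are listed by name with no severity grade.

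**Conclusion.** The point holds as a minor, free improvement. Section 7.3 states a method that ignores ordering, although a better one is named in the same section. Under proportional odds ratios of 3 to 4 at 26 per arm, the loss against Mann-Whitney is nil with 2 levels, about 8 to 10 points with 3, about 22 to 23 with 5 and about 40 to 48 with 11. These sizes rest on assumed scales, distributions and effects. The direction was the same in every setting tested with 3 or more levels.

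The documents do not support reading this as a threat to the trial's main result. Length of stay falls under the t test or Mann-Whitney rule, and no listed secondary outcome is shown to be affected.

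**What to change.** Replace the sentence on ordinal and nominal data in section 7.3 with:

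*Nominal data will be compared with the chi-square test. Ordinal data (for example pain scores) will be compared with the Mann-Whitney test, or a linear-by-linear trend test for tables with few levels.*

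This also settles which rule covers pain scores. The cost is one sentence, agreed before unblinding.

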## **8. DATA SECURITY & HANDLING**

### **8.1 DETAILS OF WHERE RECORDS WILL BE KEPT & HOW LONG WILL THEY BE STORED**

The information to be stored during and after this RCT will be in the form of password protected electronic computer files on a dedicated hard drive in the department of  
**Study Name:** A Prospective Multicentre Randomized Controlled Trial of Standard Compared to Goal-directed Therapy (GDT) for Patients Undergoing Pancreaticoduodenectomy 22

anaesthesia. Data will be password protected on a dedicated storage file set up by the Information Technology department at Austin Hospital. Only the principle investigators will have access to this electronic database. Any paper data will be locked in dedicated research storage drawers in the department of anaesthesia.

All data records both electronic and paper will be retained for 15 years prior to destruction/shredding in accordance with Good Clinical Practice for clinical trials. Information will be disposed of securely by shredding of paper documents and permanent erasure of electronic data. Any back up in the form of CD disc/DVD's will be destroyed.

## 8.2 CONFIDENTIALITY AND SECURITY

Data will be password protected on a dedicated storage file set up by the Information Technology department at Austin Hospital. Only the principle investigators will have access to this electronic database. Any paper data will be locked in dedicated research storage drawers in the department of anaesthesia.

### Study organization

This study will be managed and coordinated by a team of clinician researchers with experience in the conduct of perioperative clinical trials. The Department of Anaesthesia Research Group will centrally manage the project.

### Timelines and milestones

| Date       | Anticipated Project Milestone                             |
|------------|-----------------------------------------------------------|
| April 2013 | Ethics application and subsequent regulatory requirements |
| June 2013  | Commence recruitment                                      |
| May 2015   | Database lock, data analysis and initial results          |
| Dec 2015   | Publication                                               |

### Detailed Budget

| Item                                              | Year 1 |
|---------------------------------------------------|--------|
| Cost of FloTrac Devices @\$150each
X 52devices | 7770   |

### Maintenance

**Study Name:** A Prospective Multicentre Randomized Controlled Trial of Standard Compared to Goal-directed Therapy (GDT) for Patients Undergoing Pancreaticoduodenectomy

23

| Item                                        | Year 1 |
|---------------------------------------------|--------|
| Computer consumables (printing, paper, ink) | 500    |
| Professional statistical consultation       | 2,000  |

#### Other Items

| Item                                                            | Year 1          |
|-----------------------------------------------------------------|-----------------|
| Fee to Human Research Ethics Committees: Investigator initiated |                 |
| Total (AUD)                                              |                 |
|                                                                 | \$10,270 |

## 9. APPENDIX

### List of Attachments included:

| Document Name                                            | Version Number | Date (e.g., 18 January 2012) |
|----------------------------------------------------------|----------------|------------------------------|
| Edwards Lifesciences EV 1000 Clinical Platform           | 1              | 21 Jan 2013                  |
| Edwards Lifesciences 3 rd generation SOFTWARE | 1              | 21 Jan 2013                  |
| Edwards Lifesciences Flotrac Algorithm                   | 1              | 21 Jan 2013                  |

